### Normal video group

Participants in the normal video group will receive a 25-min of HIV education video intervention downloaded from the website of the Chinese CDC. And it is a popular science propaganda video, which lacks a storyline and is not specifically aimed at older people. Video length time and duration are the same as the *Sunset Without AIDS* group. The video contains the similar educational contents as the *Sunset Without AIDS*.

### Lecture group

Participants will receive health education lecture related to AIDS once a week for 25 min each time. An AIDS expert will hold a health lecture on AIDS prevention, and the educational content of the lecture is the similar as that in the videos. The whole lectures will be carried out once a week for 2 weeks.

### Contamination and intervention fidelity

To help ensure intervention fidelity and reduce contamination, we developed and revised multiple strategies. Some of the key strategies are listed in Table 2.

**Table 2 Tab2:** Key strategies to ensure intervention fidelity and reduce contamination

- Increased sample size up to 10% - The study group will discuss the types, scope and measures of reducing possible contamination sources through discussion and literature review - Training of trial staff and health workers to emphasize the effects of contamination. How to avoid it, how to use unbiased explanations to solve the problem - Different intervention groups will be delivered in separate areas - Intervention videos are kept by designated personnel and not available through other channels - Information packs with *Sunset Without AIDS* materials are clearly labeled and stored separately from normal video groups’ materials - Level and extent of participants reported contamination are measured at follow-up visits - Participants will be escorted before grouping and between survey locations - Field study team members confirm that trial participants only receive the specified intervention - Participants are randomly assigned to different groups by selecting envelopes - The data analysts are blinded to the allocation - Ensure that the educational content and duration of the video downloaded from the website of the Chinese CDC is the same as that of *Sunset Without AIDS* - Lecture group will be conduct by an AIDS expert for the same amount of time and content as the intervention group - Intervention sessions audio recorded, and 10% reviewed centrally [23] - All trial investigators will remain blinded	

### Assessments

Once participants’ eligibility is determined, they will be scheduled for baseline assessment. All participants will receive a face-to-face questionnaire independently. After 2 weeks of intervention, the participants will be assessed with the same questionnaire while evaluating the method to acquire relating knowledge of HIV prevention and acceptability of intervention. We will also assess participants using the same questionnaire at 1, 3, and 6 months follow-up after the intervention. All the questionnaires will be provider-administered by interviewers who are independent from the trial, i.e., interviewer asks the participant directly and types in answer. A schedule of enrolment, interventions, and assessments are outlined in Table 3.

**Table 3 Tab3:** Trial outcomes and schedule of assessments

Measures	0	BL	2 weeks	1 month	3 months	6 months
Recruitment	x					
Eligibility screen	x					
Informed consent	x					
Allocation	x					
Intervention	x					
Demographics		x				
Acceptability			x			
HIV-related knowledge		x	x	x	x	x
HIV-related stigma attitude		x	x	x	x	x
HIV-related behaviors attitude		x	x	x	x	x
HIV-related behaviors		x		x	x	x
Participant satisfaction			x			
Trial fidelity and contamination			x		x	x

### Outcomes and data collection

The primary outcome is HIV-related knowledge; the secondary outcomes comprise HIV-related stigma attitude, HIV-related behaviors attitude, and HIV-related behaviors. The assessment will be conducted in 2 weeks and 1, 3, and 6 months after the second intervention. At the same time, the acceptability and the method to acquire relating knowledge of HIV prevention will be also evaluated after 2 weeks.

HIV-related knowledge will be assessed through a questionnaire. The item of the questionnaire is designed according to the part of the contents for older people in the Core Knowledge of AIDS Prevention And Control Publicity And Education [24] issued by Chinese CDC. There are 10 items in total, one point for a correct answer. The higher the score means the more knowledgeable participants have learned. Six experts were invited to verify the content validity of this questionnaire. The results showed that the item-level CVI (I-CVI) and the scale-level CVI (S-CVI) were both 1.000.

HIV-related stigma attitude will be assessed through the Chinese version of Zelaya’s HIV/AIDS Stigma Scale, which was firstly compiled by Zelaya [25]. The scale, which included 24 items in total, was sinicized by Xing Haiyan in 2014 [26]. In the Chinese version of Zelaya AIDS Discrimination Scale, the Cronbach’s *α* coefficient of the scale was 0.91, and the Cronbach’s *α* coefficient of each dimension was 0.79–0.87. It consisted of four dimensions (fear of infection, stigma prejudice, personal discrimination, social discrimination), with six items for each dimension, a total of 24 items. There were 18 negative items and 6 positive items, and the answers were strongly agree, agree, uncertain, oppose, and strongly disagree. Six positive items are recorded as 1, 2, 3, 4, and 5 points in turn, while 18 negative ones are the opposite. The higher the score of discriminatory attitude, the more serious AIDS discrimination.

HIV-related behaviors attitude will be assessed through an eight-item questionnaire, with one point for each correct answer. The higher the score, the lower the risk of participants engaging in AIDS-related behaviors. Similarly, the content validity of the questionnaire was evaluated, the item-level CVI (I-CVI) was 0.830–1.000 and the scale-level CVI (S-CVI) was 0.875. AIDS-related behaviors will be assessed for whether and how often participants have risk behaviors related to AIDS risk. The fewer AIDS-related risk behaviors the participants have, the better their ability to prevent HIV/AIDS will be.

The HIV-related behaviors will be assessed at 2 weeks later and 1, 3, and 6 months of follow-up after the intervention. The assessment included whether they had sought sexual partners commercially or online and whether they had sex with strangers.

### Statistical analyses

All questionnaires will be administered at baseline, and the final analyses will be adjusted for the baseline scores. Descriptive statistics will be used to show the baseline characteristics of each arm. The outcome measure (HIV-related knowledge, HIV-related behaviors attitude, and HIV-related behaviors) is a binary variable, and it will be compared by chi-square tests among the three arms at 2 weeks later and 1, 3, and 6 months of follow-up. To measure the HIV-related stigma attitude outcome, analysis of variance (ANOVA) will be used to find out whether there are differences among the three arms after 2 weeks of intervention. Repeated measures ANOVA will be used to measure the HIV-related stigma attitude score at 1, 3, and 6 months of follow-up. A Bonferroni correction will be used for multiple testing. Intention-to-treat analysis will be used to account for the influence of attrition. *P* ≤ 0.05 will be deemed statistically significant. All analyses will be performed using SPSS software.

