### Recruitment of participants

We will recruit 450 older men in multiple communities through on-site recruitment. In order to keep the baseline consistent, we have purposefully pre-selected three towns, Fangshan, Jiangbei, and Kuangchang. They are the most representative and have basically the same economic, cultural, and population levels in Luzhou city. In Chinese administrative divisions, each town contains 10–20 communities. In order to facilitate the implementation of intervention, two or three communities will be selected using simple random sampling from each town, and a total of 150 older men will be recruited from these communities in one town. The trial will be held in the residents’ activity centers of three communities (Fangshan community of Fangshan Town, Kuangchang community of Kuangchang town, and Jiangbei community of Jiangbei town).

Participants who sign up will be screened; for those who meet the inclusion criteria, we will issue informed consent to them and inform them in detail of the study purpose and process, number of participants, study duration, potential risks and benefits, random allocation, data confidentiality, etc. All information and written notices will be in Chinese. When the participants agree to join in the research and complete the follow-up measurement, an informed consent form will be signed for confirmation. If the participant is unable to read, the staff will read the informed consent to the participant in full and the participant will mark his or her own fingerprint to express consent; the entire process must be witnessed by a third party not involved in the trial.

To be eligible for trial participation, individuals must meet all the following inclusion criteria:
Male aged over 60 years oldClear consciousness, no mental illness and serious visual impairment, have certain reading ability and language expression abilityPlans to stay in the trial catchment area for over 6 months

Exclusion criteria include any of the following:
Ongoing or already on HIV education interventionCognitive and mental impairment and inability to communicate properlyImpaired vision or blind

The drop out criteria includes any of the following:
Have a serious illness during the experimentDeathOther irresistible factors, for example, infectious disease isolation

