### Randomization and allocation concealment

Individual randomization will be used in allocation. Participants will be randomly assigned to one of the three intervention groups on a 1:1:1 basis. Opaque envelopes will be prepared for randomization. In 450 envelopes, each will contain a note with the words “*Sunset Without AIDS* intervention group” or “Normal video group” or “Lecture group” (150 envelopes per group). A statistician will be responsible for the generation of random sequence numbers and place them on a sequential list that will be maintained by the trial coordinator. Participants (*n* = 450) will be randomly assigned a computer-generated random number from 1 to 450, and they will randomly select an envelope in the numbering order. For each envelope selected by participants, the total number of envelopes will be reduced by one until all 450 are achieved. Participants will be randomly allocated to the different groups with a closed envelope and supervise from a third party. Separate research staff will record the allocation information of the participants. Another staff will assign participants to interventions. These staff members were not involved in the data collection and analysis process. The data analysts are blinded to the allocation. All interviewers are not involved in delivering the intervention, so they will also remain blinded.

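### The named tests carry no town term although recruitment is fixed at 150 men per town: valid under individual randomisation, but a small, avoidable loss of precision

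*Protocol article*

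**What the plan says.** All references are to the protocol article.

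- **Recruitment of participants.** Three towns are chosen in advance, two or three communities are sampled in each, and "a total of 150 older men will be recruited from these communities in one town". The towns were picked because "They are the most representative and have basically the same economic, cultural, and population levels in Luzhou city".
- **Randomization and allocation concealment.** "Individual randomization will be used in allocation", and "Participants will be randomly assigned to one of the three intervention groups on a 1:1:1 basis". There is one pool: "In 450 envelopes, each will contain a note with the words" naming one of the three arms, 150 envelopes per arm. No stratification by town is described.
- **Statistical analyses.** "the final analyses will be adjusted for the baseline scores". For knowledge (the primary outcome), behaviours attitude and behaviours, "it will be compared by chi-square tests among the three arms". For stigma, "analysis of variance (ANOVA) will be used to find out whether there are differences among the three arms after 2 weeks of intervention", with repeated measures ANOVA at 1, 3 and 6 months. Town is not mentioned.
- **Methods/design.** To limit contamination, the three groups are said to come from separate areas. Table 2 says only that the interventions are delivered in separate areas.

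**The concern.** Town is a recruitment block with a fixed quota, known for every man before he draws an envelope. If towns differ in HIV knowledge or stigma, two things follow when town is left out. The between-town variance stays in the error term, and any chance excess of one town in one arm stays in the estimated arm difference. The stated similarity of the towns concerns economic, cultural and population levels. It says nothing of HIV knowledge or stigma, and no figure is given.

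The section also fixes the method closely enough for this to be more than detail left to a later plan. It names the adjustment and a test for each outcome. A plain three-arm chi-square test has no place for a covariate, so town could enter the primary analysis only if that test were replaced. What is at stake is precision, the handling of a visible imbalance, and the avoidance of a later, data-driven decision to adjust.

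**Working it through.** **1. The plan's own figures.** The 135 per group (Sample size and adherence) cannot be reproduced, because no effect size, SD or rates are given. Back-solving with an assumed two-sided alpha of 0.05 and 80% power: d = (1.960 + 0.842) × √(2/135) = 0.341 SD. The step to 150 does reproduce with the 10% of Table 2: 135 / (1 − 0.10) = 150.

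**2. Arm-by-town imbalance under one pool of 450.** Each of the nine cells has mean 150 × 1/3 = 50 and SD √(150 × 1/3 × 2/3 × 300/449) = 4.72. In 20,000 random allocations, at least one cell was off by 10 or more in 25%. The gap between two arms within one town had SD 8.15, so a 95% range of about ±1.96 × 8.15 = ±16 men.

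**3. What the imbalance does to an arm contrast.** Let ρ be the between-town share of outcome variance (an assumption; the protocol gives none). In 4,000 simulated allocations per ρ, the chance shift in an arm difference had SD 0.016, 0.026 and 0.037 outcome SD at ρ = 0.02, 0.05 and 0.10. The detectable difference is 0.341. These shifts average to zero.

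**4. Power, with no baseline adjustment.** Removing town scales the SD by √(1 − ρ), so power = Φ(2.802/√(1 − ρ) − 1.960):

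| ρ (assumed) | Power without town | Power with town | Equivalent n for 135 |
|---|---|---|---|
| 0.01 | 80.0% | 80.4% | 134 |
| 0.02 | 80.0% | 80.8% | 133 |
| 0.05 | 80.0% | 82.0% | 129 |
| 0.10 | 80.0% | 84.0% | 122 |

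**5. With the baseline score in the model.** Assume town means of −s, 0, +s on the 0–10 knowledge score, within-town SD 2, the same town shift at baseline and follow-up, and within-town correlation r = 0.5. The between-town variance is v = 2s²/3.
- Without baseline, the ratio of variance with town to variance without is 4/(4 + v).
- With baseline, it is 4(1 − r²) / [4 + v − (4r + v)²/(4 + v)].

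| s | v | Ratio, no baseline | Ratio, baseline in model |
|---|---|---|---|
| 0.25 | 0.042 | 0.990 (1.0% saved) | 0.997 (0.3% saved) |
| 0.5 | 0.167 | 0.960 (4.0% saved) | 0.987 (1.3% saved) |
| 1 | 0.667 | 0.857 (14.3% saved) | 0.955 (4.5% saved) |

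For s = 1 with baseline: 4.667 − 2.667²/4.667 = 3.143, and 3/3.143 = 0.955. Over r from 0.3 to 0.7 the saving is 0.2–0.6%, 0.7–2.1% and 2.5–7.1% for the three shifts. If the towns are identical, adding town costs under 1% (simulated ratio 1.007).

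**6. Validity without town.** Simulated type I error of the three-arm F test was 0.046 to 0.055 over ρ from 0 to 0.10. With 4,000 runs the Monte Carlo SE is √(0.05 × 0.95/4000) = 0.003, so this is nominal.

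**7. If arm equals town instead.** The design matrix for three towns plus two arm contrasts then has rank 3 of 5, so arm and town effects cannot be separated. With 150 men per cluster the design effect is 1 + 149ρ, which is 2.5, 4.0 and 8.5 at ρ = 0.01, 0.02 and 0.05. A nominal 5% pairwise test would have about 21%, 33% and 50% type I error, and no town term repairs that.

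**The case against.** The strongest reply is that nothing here is an error. The article is condensed, it does not say that baseline scores are the sole adjustment, and a covariate list is often left to a statistical analysis plan. Allocation is not stratified by town, so the usual duty to carry a stratification factor into the model does not arise. Chance imbalance is already allowed for in the standard error. The towns were chosen to be alike, and a baseline score absorbs much of any town difference. The one scenario with a sizeable gain puts the outer towns 2 points apart on a 10-point scale, which no figure in the protocol supports.

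Most of this stands, and it sets the size of the point: a question of efficiency, and a small one. Two parts do not remove it. First, the article states the test for the primary outcome, and that test can carry neither town nor the promised baseline adjustment. If the chi-square test is run as written, the figures in step 4 are the closer guide; if the baseline promise is kept, those in step 5 are. Second, similarity of the towns on economic, cultural and population levels is not evidence of similarity on the outcomes.

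The reply that the remedy is premature also has force. A town term presumes that all three arms occur in each town, and the separate-areas statement puts that in doubt.

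**Conclusion.** The point holds as a modest recommendation. Under the individual randomisation described, leaving out town costs about 0.4 to 2 power points for ρ of 0.01 to 0.05 and about 4 points at 0.10, relative to an unadjusted analysis. It costs less once the baseline score is in the model. The values of ρ, the town shifts, the SD of 2 and the correlation of 0.5 are all assumptions.

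Three stronger readings might be inferred, and the document supports none of them:
- **That the arm comparison is biased or its type I error inflated.** With individual randomisation from one pool it is neither (step 6).
- **That the analysis ignores a stratification factor.** No stratification by town is described.
- **That about 14% of the variance is being wasted.** That figure needs a large assumed town difference and no baseline adjustment; with the baseline score it is about 4.5%.

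Whether the arms follow areas is a separate and potentially much larger question. The text conflicts on it, so it cannot be taken as settled that arm equals town.

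**What to change.** 1. Reconcile the separate-areas statement in Methods/design with the individual randomisation in Randomization and allocation concealment. State whether each town contains all three arms.
2. If it does, say in Statistical analyses that every between-arm analysis includes town as a fixed factor (2 df) alongside the baseline score. Use a linear model for the knowledge, behaviours attitude and stigma scores. For yes/no risk behaviours, use a logistic model or a Cochran-Mantel-Haenszel test stratified by town; only the logistic model also carries the baseline value.
3. If each arm is one town, do not add the term. It cannot be estimated, and the confounding must be dealt with as its own issue.

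The cost is a sentence or two of analysis wording, 2 df out of about 450, and a precision loss under 1% if the towns are identical. Recruitment, allocation and data collection do not change. The wording should be fixed before any comparison by arm is seen.

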For these dropouts, i.e., those not reaching endpoint, will be counted as failures but analyzed intention-to-treat. It will be counted as having the average score on knowledge score, behavior attitude score, and the stigma scale.

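### Knowledge (primary) and behaviors attitude are defined as sum scores but analysed as binary by chi-square, with no cut-off and a test that cannot carry the promised baseline adjustment

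*Protocol article*

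**What the plan says.** Under Outcomes and data collection: "The primary outcome is HIV-related knowledge". Its instrument is a questionnaire: "There are 10 items in total, one point for a correct answer". The direction is graded, with no pass mark: "The higher the score means the more knowledgeable participants have learned". The attitude measure is built the same way: "HIV-related behaviors attitude will be assessed through an eight-item questionnaire, with one point for each correct answer".

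The dropout rule at the end of Recruitment of participants also treats both as scores: "It will be counted as having the average score on knowledge score, behavior attitude score, and the stigma scale".

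Statistical analyses then states: "The outcome measure (HIV-related knowledge, HIV-related behaviors attitude, and HIV-related behaviors) is a binary variable, and it will be compared by chi-square tests". This comparison covers all arms and is repeated at each of the four follow-up visits. The opening sentence of that paragraph promises that "the final analyses will be adjusted for the baseline scores". The paragraph also specifies ANOVA and repeated-measures ANOVA for stigma, a Bonferroni correction, and a significance threshold of P "≤ 0.05 will be deemed statistically significant". It names no regression, ANCOVA, logistic or stratified method.

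**The concern.** A 0–10 sum and a 0–8 sum are not binary variables. To run the chi-square test as written, the analyst has to add a rule that the protocol does not contain: either a cut-off on each score, or item-by-item testing, which for knowledge means 10 items × 4 visits = 40 tests. These routes can lead to different conclusions from the same data, and for knowledge this is the primary outcome.

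The second difficulty is internal to the statistics paragraph. A chi-square test comparing three arms has no place for a covariate, so the only method named for these outcomes does not deliver the adjustment promised a few lines earlier. Baseline scores are collected on every participant, so the information for a sharper comparison is at hand.

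**Working it through.** **1. The definitions side by side**

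| Measure | Outcomes and data collection | Dropout rule | Statistical analyses |
|---|---|---|---|
| Knowledge (primary) | sum of 10 one-point items | has an average score | binary, chi-square |
| Behaviors attitude | sum of 8 one-point items | has an average score | binary, chi-square |
| Behaviors | whether, and how often, risk behaviors occurred | not given an average | binary, chi-square |

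Only the third row can reasonably be binary as it stands. The first two conflict.

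**2. The plan's own figure.** Sample size and adherence gives 135 per group for 80% power, raised to 150. The increase is consistent with the 10% in Table 2: 135 / (1 − 0.10) = 150. The 135 cannot be reproduced forward, because no effect size, SD or proportion is given. Solving backwards for two arms at two-sided 0.05 (sidedness assumed):

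- as means: d = (1.960 + 0.842) × √(2/135) = 0.341 SD;
- as proportions: 30% v 46.5%, 40% v 57%, 50% v 66.7%, 60% v 75.8% or 70% v 84.3%.

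At a Bonferroni level of 0.05/3 it fits 0.394 SD or 50% v 69.2%. So 135 does not reveal whether a score or a proportion was planned.

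**3. Information kept after splitting a normal score.** With a proportion p above the cut c, relative efficiency = φ(c)² / [p(1 − p)].

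- p = 0.5: 0.3989² / 0.25 = 0.637
- p = 0.3: 0.576
- p = 0.2: 0.2800² / 0.16 = 0.490
- p = 0.1: 0.342

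**4. Illustration of power.** Assume d = 0.341, which gives 80% on the score at 135 per arm, and a normal score. The proportion above the cut in the better arm is 1 − Φ(c − 0.341). Two-proportion power then gives:

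| Controls above cut | Better arm above cut | Power, 135 per arm | Power, 150 per arm | n per arm for 80% |
|---|---|---|---|---|
| 50% | 63.3% | 60% | 65% | 216 |
| 30% | 42.7% | 59% | 63% | 224 |
| 20% | 30.8% | 53% | 58% | 253 |
| 80% | 88.2% | 45% | 49% | 316 |

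The large-sample formula gives almost the same at the median: Φ(2.802 × √0.637 − 1.960) = 61%. Hence the range 45–61%. The score itself has 80% at 135 and 84% at 150.

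**5. Baseline adjustment.** ANCOVA power = Φ(2.802 / √(1 − r²) − 1.960). The correlation r is not in the protocol, so a range is shown: 84% at r = 0.3, 90% at r = 0.5 and 98% at r = 0.7 (135 per arm). At r = 0.5 and 150 per arm it is about 93%.

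**6. Check on a bounded, whole-number score.** A simulated 0–10 score (mean 6, SD 2, rounded and truncated, same shift, 135 per arm, r = 0.5, 3,000 runs per cut-off) gave chi-square power of 59%, 60%, 56% and 41% at pass marks of 6, 7, 8 and 9. The t-test gave 78–79% and ANCOVA 87–89%. The normal approximation is therefore not driving the result.

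**The case against.** The strongest reply is that this is a condensed article. A full protocol or statistical analysis plan may exist, and could define a pass mark and an adjusted categorical method, such as a stratified chi-square test or logistic regression. On that view, the adjustment sentence governs and the test is only loosely named. The dropout rule also counts men who do not reach the endpoint as failures, which suggests that a pass/fail reading was in mind. This has some force: a missing cut-off or model alone would be no finding. It does not remove the conflict, because the text shown calls a sum score binary and names a test that does not do what its own paragraph promises.

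Four stronger readings are tempting, and the document does not support them.

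- *The trial loses planned power.* The sample size section gives no effect size, and 135 fits proportions as well as means. If proportions were planned, no planned power is lost.
- *The stigma analysis has the same fault.* Stigma is analysed as a score, and both ANOVA and repeated-measures ANOVA can take a baseline covariate. The method sentence simply does not repeat it.
- *Separate tests at each visit are invalid.* A comparison of arms at one visit is valid despite correlation within a man, and the stated Bonferroni correction holds under any dependence.
- *The cut-off will be chosen to suit the results.* Enrolment began in June 2021 and no cut-off is printed, but the data analysts are stated to be blinded to allocation. The risk is an unfixed choice; nothing suggests misuse.

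**Conclusion.** The point holds for knowledge and behaviors attitude. The primary analysis cannot be run on the primary endpoint without a rule that the protocol does not state, and the named test cannot supply the promised baseline adjustment. Neither conclusion depends on any assumption.

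The size does depend on assumptions. If the score is roughly normal, splitting it keeps at most about 64% of its information, and less with an off-centre cut. The power figures (about 45–61% after splitting, against 80% on the score and about 90% with adjustment) further assume a 0.341 SD difference, a two-arm comparison at two-sided 0.05 and a baseline correlation of 0.5. They compare methods; they do not estimate this trial's power.

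**What to change.** Replace the chi-square sentence for knowledge and attitude with a baseline-adjusted analysis of the score: either ANCOVA at each visit, or a linear mixed model over the four visits with arm, visit, arm-by-visit and baseline score. Report adjusted mean differences with 95% confidence intervals. If the mixed model is chosen, say whether the average-score rule for dropouts still applies.

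- Keep a binary analysis for the yes/no behaviors, using logistic regression or GEE with baseline behavior as a covariate.
- State that the stigma ANOVAs include the baseline score as a covariate.
- If a proportion counted as knowledgeable is wanted, fix the cut-off before unblinding and label the result supportive.
- Include town only if men are randomised within towns. Methods/design says the three groups come from separate areas, while Randomization and allocation concealment says individuals are randomised. If arm and town coincide, a town term cannot be estimated, so these two statements need reconciling first.
- State the effect size behind 135 on the scale of the endpoint chosen.

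No new data or participants are needed. The cost is an amendment to the ethics committee and the registry, as Ethical considerations requires for important modifications.

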### Sample size and adherence

The sample size calculation is based on the primary outcome, i.e., HIV-related knowledge. The sufficient statistical power to detect changes in HIV-related knowledge after the intervention were considered in sample size calculation, and 135 participants were need in each group to maintain 80% statistical power. Considering this sample size was also powered for the secondary outcomes and the attrition rate, the sample size of each group was determined to be 150, and the total sample size was 450.To motivate participants to stay in the trial, we would use intrinsic reward to help 450 participants adhere to the intervention and follow-up. Participants would receive some prizes for each assessment. In addition, after completing the research, each participant would also receive a reward of 50 RMB in cash.

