## Intervention group overview

### *Sunset Without AIDS* intervention group

Participants in the *Sunset Without AIDS* intervention group will receive a 25-min intervention. They will be required to watch the *Sunset Without AIDS* video once per week for 2 weeks. During the broadcast, a member of research team will be responsible for answering questions. After 2 weeks of intervention, the effect of the intervention will be evaluated using the same questionnaire as applied in the baseline survey.

To ensure the compliance of participants, participants will be recognized and rewarded after completing two video viewing sessions and 2-week follow-up assessments.

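### The planned tests treat the men as independent, yet the education appears to be given in shared sessions; any positive within-session correlation makes P values too small and the 80% power overstated

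*Protocol article*

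**What the plan says.** Under Randomization and allocation concealment, the protocol article states: "Individual randomization will be used in allocation". Delivery is then described in terms that point to groups:

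- Lecture group: "An AIDS expert will hold a health lecture on AIDS prevention", weekly for two weeks.
- *Sunset Without AIDS* group: "During the broadcast, a member of research team will be responsible for answering questions". The normal video group has the same length and duration.
- Recruitment of participants: "The trial will be held in the residents’ activity centers of three communities", for 450 men in total.
- Table 2 (Contamination and intervention fidelity): "Different intervention groups will be delivered in separate areas". The same table provides for audio recording of intervention sessions, with 10% reviewed centrally.

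The number of sessions, their size and who leads them are not given.

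Statistical analyses names the tests. For knowledge (the primary outcome), behavior attitude and behaviors, "it will be compared by chi-square tests among the three arms at 2 weeks later and 1, 3, and 6 months of follow-up". Stigma is compared by ANOVA at 2 weeks and by repeated measures ANOVA at 1, 3 and 6 months. Baseline adjustment and a Bonferroni correction are mentioned. No term for session appears.

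Sample size and adherence says that "135 participants were need in each group to maintain 80% statistical power", raised to 150 with reference to secondary outcomes and attrition. No ICC or design effect is mentioned.

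**The concern.** When individually randomized people are treated in groups, the group forms after allocation and becomes part of the treatment. Men in one session share the lecturer or question-answerer, the questions raised and the discussion, so their later scores may be more alike than those of men from different sessions. Randomization does not remove this, because the correlation arises after it.

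Chi-square and ANOVA set that correlation to exactly zero. Repeated measures ANOVA allows for correlation between visits of the same man, not between men. Neither baseline adjustment nor a Bonferroni correction addresses it.

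At stake are the false-positive rate of the primary comparison and the meaning of the stated 80%. The lecture comparison is the most exposed, since a live speaker's performance is common to everyone in the room.

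**Working it through.** **The plan's own figure.** The 135 cannot be reproduced, because the article gives no effect size, SD or rates. Working backwards with a two-sided 5% level (sidedness is not stated) and 80% power, 135 per arm corresponds to a standardized difference of (1.960 + 0.842) × √(2/135) = 0.341, or for example to 40% versus 57%. Neither involves a design effect. The step to 150 equals a 10% loss allowance alone: 135 / 0.90 = 150.

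**Inputs.** From the article: 135 and 150 per arm, 80% power, 5% level, three arms. Assumed, because the article gives neither: session size m of 15, 30 or 50, and ICC of 0.01, 0.02 or 0.05, the same in all arms.

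**Formulas.**

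- Design effect: DE = 1 + (m − 1) × ICC.
- True error of the nominal 5% three-arm chi-square (2 df): P(χ² > 5.991/DE) = exp(−2.996/DE).
- True error of a two-arm comparison: 2 × [1 − Φ(1.96/√DE)].
- Power at 135 per arm with correct standard errors: Φ(2.80/√DE − 1.96).

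Smallest case: DE = 1 + 14 × 0.01 = 1.14, and exp(−2.996/1.14) = 0.072. Largest case: DE = 1 + 49 × 0.05 = 3.45, and exp(−2.996/3.45) = 0.420.

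| m | ICC | DE | Three-arm error | Two-arm error | Power at 135 |
|---|---|---|---|---|---|
| 15 | 0.01 | 1.14 | 7.2% | 6.6% | 74.7% |
| 15 | 0.02 | 1.28 | 9.6% | 8.3% | 69.7% |
| 15 | 0.05 | 1.70 | 17.2% | 13.3% | 57.5% |
| 30 | 0.01 | 1.29 | 9.8% | 8.4% | 69.4% |
| 30 | 0.02 | 1.58 | 15.0% | 11.9% | 60.6% |
| 30 | 0.05 | 2.45 | 29.4% | 21% | 43.2% |
| 50 | 0.01 | 1.49 | 13.4% | 10.8% | 63.1% |
| 50 | 0.02 | 1.98 | 22.0% | 16.4% | 51.2% |
| 50 | 0.05 | 3.45 | 42.0% | 29.1% | 32.6% |

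The effective size of 150 men per arm is 150/1.14 = 132 in the smallest case and 150/3.45 = 43 in the largest.

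**Check by simulation.** Beta-binomial data with a true proportion of 0.6 in every arm and 20,000 runs per setting gave three-arm error rates of 0.051 to 0.053 with essentially no correlation. Over ICC 0.01 to 0.05 the rates were 0.073 to 0.175 (10 sessions of 15 per arm), 0.103 to 0.298 (5 of 30) and 0.132 to 0.428 (3 of 50). These agree with the formula.

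**If only the lecture arm is correlated.** In a lecture-versus-video comparison the variance is then inflated by (DE + 1)/2. That is 1.07 to 2.225 over the same range, giving a two-arm error of 2 × [1 − Φ(1.96/√1.07)] = 5.8% up to 2 × [1 − Φ(1.96/√2.225)] = 18.9%. The video-versus-video comparison would be unaffected.

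**The case against.** **The inputs are unknown.** Session size and ICC are nowhere in the article, and group delivery is inferred rather than stated. This stands: the finding is conditional and the magnitude is a range under assumptions. It does not justify the one value that the stated tests impose, zero. A condensed article may leave session structure and ICC to the full protocol or analysis plan, but the tests themselves are stated here.

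**Two arms show a fixed recording, and men are questioned individually.** This also stands. Correlation may be smaller in the video arms, and the table then overstates the problem for comparisons that involve them.

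**A reader might infer one screening per arm.** The text does not say so. Central review of 10% of sessions suggests several.

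**A reader might infer that recruitment by community and town also inflates the error, since** "two or three communities will be selected using simple random sampling from each town". Under truly individual randomization it does not, because communities are then balanced across arms by chance. A simulation of 450 men from 8 communities, individually randomized (20,000 runs), gave a three-arm error of 0.050 at a community ICC of 0.01 and 0.051 at 0.05.

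**A reader might infer that each arm is one town.** Methods/design has the groups coming from separate areas, and 150 men per town matches 150 per arm. But the randomization section describes individual allocation from one pool of 450 envelopes, and Table 2 speaks only of where the interventions are delivered. The sections do not settle the matter and must be reconciled.

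**Conclusion.** The concern holds in conditional form. The stated analysis assumes zero correlation between men who appear to share sessions, and the sample size shows no allowance for it beyond a step that 10% loss alone would use up. With a within-session correlation above zero, P values are too small and the 80% at 135 per arm is too high.

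Under the assumed session sizes of 15 to 50 and ICC of 0.01 to 0.05, equal in all arms, the three-arm chi-square has a true error of about 7% to 42% and power is about 75% down to 33%. These are illustrations, not estimates for this trial. The article does not support the stronger claims that each arm has a single session, that community or town clustering inflates the error under individual allocation, or that arm and town coincide.

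This should be changed before the analysis. Repair is cheap, and the result changes little if the correlation proves negligible.

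**What to change.** 1. Record a session identifier for each man or, since recruitment was due to end in December 2021, recover it from attendance records. Report the number, size and leader of sessions per arm.
2. Replace the chi-square, ANOVA and repeated measures ANOVA by a mixed model (or GEE) with arm, visit, arm-by-visit and baseline score, man and session as clustering levels, and small-sample degrees of freedom. Use a linear or logistic form according to the scale on which each outcome is analysed. SPSS offers mixed models for both.
3. Describe the 80% as power before clustering and give the range with a design effect. Do not enlarge the trial.
4. Reconcile Methods/design, Recruitment of participants, Randomization and allocation concealment, and Table 2 on whether arms are tied to areas. Add town as a covariate only if every arm is represented in every town. If an arm coincides with one area or one session, no model can separate the two, and the report must say so.
5. If one expert gives all lectures, limit the conclusion to that lecturer's lecture; a session term cannot separate expert from format.

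Cost: one identifier, a change of analysis wording and an amendment by the route under Ethical considerations. Intervals will be somewhat wider and the stated power less favourable. With few sessions, the session variance will be imprecisely estimated.
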